### Study design

Prospective longitudinal controlled human infection study after intradermal injection with BCG SSI in two phases: Phase A is designed to confirm microbiological recovery and determine agreement between the current gold standard of skin punch biopsy 14 days after injection with minimally invasive biopsy techniques. Phase B is designed to refine and optimise immunological assays to measure local (using optimal minimally invasive techniques), systemic (blood) and respiratory mucosal responses to intradermal BCG injection.

**
Phase A
**

Ten participants will receive a single intradermal injection to the upper arm of BCG SSI 6–24 × 10
^5^ colony forming units in line with an optimised and established existing protocol
^
15
^. The BCG SSI strain has been chosen as the UK licensed vaccine for TB. The dose (3x higher than that used in routine vaccination) has been chosen based on study findings by Minhinnick
*et al.*
^
15
^, who demonstrated good mycobacterial recovery at this concentration with no increase in participant adverse events between the doses. Participants will be followed up longitudinally with active assessment for tolerability; adverse events; and serious adverse events. We will determine BCG SSI recovery from the intradermal injection site 14 days later by classical microbiology and molecular diagnostic techniques using gold standard punch biopsy
^
15
^ as our primary outcome measure. In parallel, and after local anaesthetic injection, we will obtain paired minimally invasive samples (skin swab, skin scrape
^
18
^ and microbiopsy
^
17
^ from the same skin site at 14 days and determine agreement of BCG SSI recovery by classical microbiology and molecular diagnostic techniques with punch biopsy

Parameters for progression from Phase A to Phase B are:

1.Participants able to tolerate study procedures2.No experimental challenge related SAE or SUSAR detected3.Confirmation of BCG recovery by classical microbiology or molecular techniques from punch biopsy at day 14 in all 10 participants who received intradermal BCG challenge4.Confirmation of BCG recovery by classical microbiology or molecular techniques from any of the minimally invasive skin sample technique (swab, scrape and microbiopsy) at day 14 in ≥9 participants who received intradermal BCG challenge.

**
Phase B
**

Twenty participants will receive a single intradermal injection to the upper arm of BCG SSI 6–24 × 10

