### Safety reporting

**
Definition of serious adverse events
**

Our safety reporting terms and definitions are described in
Table 4

**Table 4. T4:** Safety definitions. NB: to avoid confusion or misunderstanding of the difference between the terms “serious” and “severe”, the following note of clarification is provided: “Severe” is often used to describe intensity of a specific event, which may be of relatively minor medical significance. “Seriousness” is the regulatory definition supplied above.

Term	Definition
**Adverse Event (AE)**	Any untoward medical occurrence in a participant to whom a medicinal product or challenge agent has been administered, including occurrences, which are not necessarily caused by or related to that product.
**Adverse Reaction (AR)**	An untoward and unintended response in a participant to an investigational medicinal product or challenge agent which is related to any dose administered to that participant. The phrase "response to an investigational medicinal product or challenge agent" means that a causal relationship between a trial medication/challenge agent and an AE is at least a reasonable possibility, i.e. the relationship cannot be ruled out. All cases judged by either the reporting medically qualified professional or the Sponsor as having a reasonable suspected causal relationship to the trial medication/challenge agent qualify as adverse reactions. It is important to note that this is entirely separate to the known side effects for the challenge agent. It is specifically a temporal relationship between administration of challenge agent, the half-life, and the time of the event or any valid alternative aetiology that would explain the event.
**Adverse Event of** **Special Interest ** **(AESI)**	An adverse event of special interest (serious or non-serious) is one of scientific and medical concern specific to the challenge agent, for which ongoing monitoring and rapid communication by the investigator to the Sponsor can be appropriate. Such an event might warrant further investigation in order to characterise and understand it. Depending on the nature of the event, rapid communication by the trial Sponsor to other parties (e.g., regulators, DSMC) might also be warranted.

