**Serious Adverse** **Event (SAE)**	A serious adverse event is any untoward medical occurrence that: • Results in death • Is life-threatening • Requires inpatient hospitalisation or prolongation of existing hospitalisation • Results in persistent or significant disability/incapacity • Consists of a congenital anomaly or birth defect Other ‘important medical events’ may also be considered serious if they jeopardise the participant or require an intervention to prevent one of the above consequences. NOTE: The term "life-threatening" in the definition of "serious" refers to an event in which the participant was at risk of death at the time of the event; it does not refer to an event which hypothetically might have caused death if it were more severe.
**Serious Adverse** **Reaction (SAR)**	An adverse event that is both serious and, in the opinion of the reporting Investigator, believed with reasonable probability to be due to one of the trial treatments/challenge agents, based on the information provided.
**Suspected** **Unexpected** **Serious Adverse** **Reactions (SUSAR)**	A serious adverse reaction, the nature and severity of which is not consistent with the information about the challenge agent.

**
Adverse events
**

Table 5 details the expected adverse events of BCG injection and challenge site biopsy

**
Adverse event severity assessment
**

Unexpected adverse events will be recorded and these AEs will be graded by severity as follows (where 0 = absent, 1 = mild, 2 = moderate, 3 = severe).
Table 6 details this process:

**
Causality assessment
**

The relationship of each adverse event to inoculation must be determined by a medically qualified individual within the study team according to the following definitions:

0 = No relationship:

•   No temporal relationship to BCG intradermal injection

•   Definite alternative aetiology (clinical, environmental or other intervention), and

•   Does not follow pattern of recognised response to BCG intradermal injection;.

1 = Unlikely relationship:

•   Unlikely temporal relationship to BCG intradermal injection or;

•   Alternate aetiology likely (clinical, environmental or other intervention), and

•   Does not follow pattern of recognised response to BCG intradermal injection

2= Likely relationship:

•   Reasonable temporal relationship to BCG intradermal injection, and

•   Event not readily explained by alternative aetiology (clinical, environmental or other interventions), and

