•   Similar pattern of response to that seen to BCG intradermal injection, or

3 = Definite

•   Reasonable temporal relationship to BCG intradermal injection and

•   Event not readily produced by alternative aetiology (clinical, environment, or other interventions), and

•   Known pattern of response to BCG intradermal injection.

The chief investigator (CI), with the consultation of the trial steering committee (TSC), if required, will determine causality of AEs. The greatest degree of causal relationship (definite > probable > possible > unlikely related > not related) determined by either the PI or TSC after their discussions will determine the ultimate classification of the AE. Definite (4), probable (3) and possible (2) are considered to be related. No relationship (0) and unlikely (1) are unrelated.

**Table 5. T5:** Expected adverse events.

Expected adverse events
Pain/tenderness at the injection or biopsy site
Redness at the injection or biopsy site
Swelling at the injection or biopsy site
Warmth at the injection or biopsy site
Scaling/pustules at the injection or biopsy site
Transient ipsilateral axillary lymphadenopathy <1cm diameter
Scar at challenge (and biopsy site)
Headache
Fever (>38.3°C)

**
Procedure for recording adverse events
**

Participants will be asked to complete diary cards for 14 days after BCG challenge. They will be provided with a thermometer and tape measure to enable daily recording of temperature and local reactions at the injection site.

The diary cards will be reviewed at follow up visits and adverse events recorded in the CRF. Outside the diary card periods, expected local and systemic AEs (listed in
Table 5) will be specifically asked about and graded by severity (as detailed in
Table 6). Participants will be given the opportunity to report any other new symptoms since the last visit with start and stop dates and any treatments undergone.

All AEs (whether reported by the volunteer or solicited by the Investigator) will be clinically assessed at each visit and recorded in the CRF.

The following information will be recorded: description, date of onset and end date, severity and any treatment or intervention undertaken. The severity of events will be assessed on the following scale: 1 = mild, 2 = moderate, 3 = severe.

An assessment of relatedness to the BCG challenge will then be made by the Investigator.

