AEs considered related to the BCG challenge as judged by a medically qualified investigator or the Sponsor will be followed either until resolution, or the event is considered stable.

**Table 6. T6:** Grading of adverse events.

Adverse Event	Grade	Measurement
Pain/tenderness at the injection or biopsy site	0 1 2 3	No pain at all Painful on touch, easily tolerated Painful when limb is moved, interferes with daily activity Severe pain at rest, interferes with daily activity
Redness at the injection or biopsy site	0 1 2 3	0mm 1–50mm 51–100mm >100mm
Swelling at the injection or biopsy site	0 1 2 3	0mm 1–20mm 21–50mm >50mm
Fever (oral)	0 1 2 3	≤37.5°C 37.6 – 38.0°C 38.1 – 38.9°C ≥39.0°C
Other AEs	0 1 2 3	Absence of symptom Awareness of symptom but tolerated; transient or mild discomfort; little or no medical intervention required Mild to moderate discomfort leading to interference with usual activity, some minimal medical intervention/therapy may be required. Significant interference with daily activity; some assistance usually required; medical intervention/therapy required; hospitalisation possible

**
Reporting procedures for Serious Adverse Events (SAEs) and Suspected Unexpected Serious Adverse Reactions (SUSARs)
**

Any serious adverse event considered by the CI to be related to the challenge agent and unexpected will be reported to the REC. As the challenge agents are vaccines with Marketing Authorisation, the mechanism for reporting any SAEs to the MHRA is via yellow card.

**
Follow up and outcome of adverse events
**

Those adverse events which are unexpected and likely to be related to the BCG, whether serious or not, which persist at the end of the study will be followed up by the Investigator until their resolution. Additional follow-up visits may be arranged to enable this. As appropriate, participants with ongoing AEs may be advised to consult their General Practitioner (National Health Service) or the study team will arrange specialist review within the NHS. The outcome of all related non-serious AEs and any SAEs will be assessed as:

Recovered/resolvedRecovered with sequelae/resolved with sequelaeUnknownOngoing at end of studyFatal

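### The written causality codes have no place for a well-timed, unexplained event of unrecognised pattern, although Table 4 counts such an event as an adverse reaction

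*Protocol article*

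**What the plan says.** All references are to the Protocol article.

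**Causality assessment (Safety reporting).** The codes are mandatory: "The relationship of each adverse event to inoculation must be determined by a medically qualified individual within the study team according to the following definitions". Code 2 (likely) opens with "Reasonable temporal relationship to BCG intradermal injection, and", adds that no other cause readily explains the event, and ends with "Similar pattern of response to that seen to BCG intradermal injection, or". Nothing follows that last word except code 3. Code 3 (definite) repeats the timing and alternative-cause conditions and adds "Known pattern of response to BCG intradermal injection". Codes 0 and 1 rest on poor timing, an alternative cause and the absence of a recognised BCG pattern.

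The text after the codes uses a five-level scale. It counts *possible* (2), *probable* (3) and *definite* (4) as related, and 0 and 1 as unrelated. No criteria are printed for *possible* or *probable*.

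**Table 4, adverse reaction.** The threshold is a reasonable possibility of causation, meaning that a link cannot be excluded. The judgement rests on timing and on other explanations. Of the causal judgement the table says: "It is important to note that this is entirely separate to the known side effects for the challenge agent".

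**Rules that use relatedness.**
- Ethics committee reporting: "Any serious adverse event considered by the CI to be related to the challenge agent and unexpected will be reported to the REC".
- Follow-up of events still present at study end: "Those adverse events which are unexpected and likely to be related to the BCG, whether serious or not".
- Progression from Phase A to Phase B, criterion 2 (Study design): "No experimental challenge related SAE or SUSAR detected".

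**Expectedness** has its own section and is judged against the SmPC.

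**The concern.** Codes 2 and 3 place a test of familiarity inside the test of causality. An event that follows the injection at a plausible interval, with nothing else to explain it, cannot enter either code unless it looks like something BCG is already known to do. Table 4 says that familiarity should play no part in that judgement.

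The rules for ethics committee reporting and for follow-up at study end apply to events that are both related and unexpected, and criterion 2 applies to challenge-related serious events. A reaction of a new kind is a main target of such rules, and it is the kind for which the codes offer no related category. Safety and tolerability is a stated objective, at three times the routine vaccination dose, so the classification should not depend on assessors departing from the written definitions.

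**Working it through.** No sample size or power figure bears on this point. The check applies the printed conditions to every type of event.

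**Inputs.** Timing is reasonable or poor, an alternative cause is absent or present, and the pattern is BCG-like or new: 2 × 2 × 2 = 8 combinations.

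**Rules as printed.**
- Codes 2 and 3: reasonable timing AND no alternative cause AND BCG-like pattern.
- Code 1 mixes an 'or' with an 'and', so two parsings are possible. Strict: (poor timing OR alternative cause) AND new pattern. Lenient: poor timing OR (alternative cause AND new pattern).
- Code 0 has no connector after its first condition. It is read here as needing all three conditions. A looser reading could only take in events with no temporal relationship or with a definite alternative cause.

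| Row | Timing | Alternative cause | Pattern | Strict | Lenient |
|---|---|---|---|---|---|
| 1 | reasonable | none | BCG-like | 2 or 3 | 2 or 3 |
| 2 | reasonable | none | new | no code | no code |
| 3 | reasonable | present | BCG-like | no code | no code |
| 4 | reasonable | present | new | 1 | 1 |
| 5 | poor | none | BCG-like | no code | 1 |
| 6 | poor | none | new | 1 | 1 |
| 7 | poor | present | BCG-like | no code | 1 |
| 8 | poor | present | new | 0 or 1 | 0 or 1 |

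**Result.** One of 8 combinations (row 1) can be coded related. Four of 8 have no code on the strict parsing (rows 2, 3, 5, 7) and 2 of 8 on the lenient one (rows 2, 3). Row 2 has no code on either, and no reading of code 0 reaches it.

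**Finer check.** With three levels each for timing (reasonable, unlikely, none), alternative cause (none, likely, definite) and pattern (new, similar, known) there are 3 × 3 × 3 = 27 combinations. All 9 with a new pattern fail codes 2 and 3. Reasonable timing with no alternative cause and a new pattern again has no code, whether code 0 is joined by 'and' or by 'or'.

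**Row 2 under the two sets of definitions.**

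| | Causality codes | Table 4 |
|---|---|---|
| Timing reasonable | met | met |
| No other explanation | met | met |
| Familiar BCG pattern | required, not met | not to be considered |
| Outcome | no code | adverse reaction |

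**With pattern removed as an entry condition.** Code 2 becomes reasonable timing AND no alternative cause. Rows 1 and 2 are then related (2 of 8), and only row 1 can rise to *definite*. Row 3 could be *possible*, which would make 3 of 8.

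These are counts of logical cases. They do not say how often events fall in each.

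**The case against.** **The list is visibly incomplete.** Code 2 ends in an unfinished 'or', and the *possible* level counts as related with no pattern condition attached. A condition may have been lost in condensing the article. However, nothing printed admits row 2. If the 'or' leads to code 3, that code needs a known pattern too, and a level with no criteria gives the assessor no rule to apply. Defining the missing levels would settle much of this point.

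**The downstream rules rest on judgement.** Table 4 leaves relatedness to a medically qualified professional or the Sponsor, ethics committee reporting depends on the chief investigator's view, and the higher of the PI's and TSC's ratings prevails. An assessor could therefore call a row 2 event related and be consistent with Table 4. This stands as a mitigation. It does not remove the conflict, because the causality section says that the listed definitions must be used.

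**Other safeguards ignore relatedness.** A reader might infer that the safety objective is blind to a new type of harm, or that Phase B could open after one unnoticed. The document does not support that. The DSMC reviews SAEs and AESIs whatever their relatedness and receives a report after any SAE. SAEs go to the MHRA by yellow card. All adverse events are assessed and recorded, and the SMG reviews safety reports weekly. This objection largely succeeds as to consequences. These safeguards do not, however, assign the relatedness code or decide whether criterion 2 is formally met.

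**Pattern is not the same as expectedness.** A reader might also infer that no event can be both related and unexpected in nature. That goes too far: code 2 asks for a *similar* pattern and expectedness is judged against the SmPC, so an unlisted reaction that resembles a BCG effect can be both.

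**Conclusion.** The point holds as a contradiction between two definitions in the same section. An event with reasonable timing, no alternative cause and an unrecognised pattern is an adverse reaction under Table 4 and has no code under the causality assessment. It is not forced into an unrelated code; it has no valid code at all.

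The effect is that the written codes can leave a new type of reaction out of the *related* category used for ethics committee reporting, follow-up and progression criterion 2. The exposure is mainly misclassification, and it is greatest for non-serious events: the DSMC's review regardless of relatedness covers SAEs and AESIs, and other events reach it through interim safety data or requested reviews.

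The conclusion rests on reading the conditions of codes 2 and 3 as joined by the printed 'and', and on no further code 2 condition existing in a fuller protocol. The document gives no basis for estimating how many events would be affected.

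**What to change.** Reconcile the causality codes with Table 4:

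1. Remove pattern as an entry condition for *related*. Reasonable timing and no ready alternative cause should suffice for code 2, and a recognised BCG pattern should only raise the event to *definite*.
2. Give the *possible* level a criterion based on Table 4's threshold, that a causal link cannot be ruled out. This would also provide for events with reasonable timing and a BCG-like pattern where another cause is present.
3. Complete or delete the unfinished 'or' at the end of code 2.
4. Leave expectedness to the separate assessment against the SmPC.

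The cost is a wording change in the causality section and the adverse event form. The article states that recruitment had not begun at submission. The downside is small: a few more events will be classed as related.

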Engagement with research team	STOP if the research team have concerns about participant’s ability to commit to frequent communication and safety checks
Illness during study	STOP if participant develops a medical condition or commences medication while on the study that would meet the exclusion criteria
Full blood count	STOP if Hb <10g/l STOP if total WCC <1.5 ×109/l STOP if total WCC >12 ×109/l STOP if platelets <75 ×109/l
Resting SpO _2_	STOP if < 94%

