### Participant identification

**
Study participants
**

Eligibility assessment will be completed in stages:

•   Screening: study nurse or doctor checks that as part of the consent process the potential participant meets all the general screening criteria (
Table 2).

•   Eligibility is confirmed on the screening and follow-up visits. If any STOP criteria (see
Table 3) are met, the participant is excluded from and/or exits the study. Eligibility will be signed off by a medical doctor on the eCRF prior to primary intradermal injection.

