### Exclusion criteria

Exclusion criteria will be self-reported and/or confirmed from GP questionnaire (GPQ) or medical summary if deemed necessary at research clinician discretion

•   Laboratory evidence at screening of latent M.
*tb* infection as indicated by a positive ELISPOT response to ESAT6 or CFP10 antigens
^
a
^

•   Clinical, radiological, or laboratory evidence of current active TB disease
^
b
^

•   Previous vaccination with BCG, or any candidate TB vaccine

•   Within the last year had close household contact with an individual with smear positive pulmonary tuberculosis

•   Clinically significant history of skin disorder, allergy, immunodeficiency (including HIV), cancer, cardiovascular disease, respiratory disease, gastrointestinal disease, liver disease, renal disease, endocrine disorder, neurological illness or psychiatric disorder.

•   Current medical issues

○Acute respiratory tract infection in the four weeks preceding recruitment○Any uncontrolled medical or surgical condition at the discretion of the study doctor

•   Maternal

○Female participants who are pregnant○Female participants who are lactating○Female participants who intend to become pregnant during the study○Female participants who are unable to take contraception measures during the study

•   Smoking

○Current (defined as ≥5/week) or ex-smoker (cigarettes / cigars / e-cigarette / vaping / smoking of recreational drugs) in the last 6 months.○Previous significant smoking history (more than 20 cigarettes per day for 20 years or the equivalent [>20 pack years]).

•   Current alcohol and recreational drug use

○Regularly drinks ≥3units/day (male) or ≥2units/day (female)○Uses recreational drugs○Participants may be excluded at the discretion of the research clinician

•   Concurrent oral or systemic steroid medication or the concurrent use of other immunosuppressive agents

•   History of anaphylaxis to vaccination or any allergy likely to be exacerbated by any component of the challenge agent

•   Has received any vaccination within one month of screening visit.

•   Has not completed at least two COVID-19 vaccination doses

•   Any abnormality of screening blood or urine tests that is deemed to be clinically significant or that may compromise the safety of the volunteer in the study
^
b
^

•   Positive HBsAg, HCV or HIV antibodies

•   Current involvement in another trial that involves regular blood tests or an investigational medicinal product
^
c
^

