•   Use of an investigational medicinal product or non-registered drug, live vaccine, or investigational medical device for four weeks prior to dosing with the study challenge agent

•   Administration of immunoglobulins and/or any blood products within the three months preceding the planned challenge date

•   Participants who meet STOP criteria at the time of screening (see
Table 3)

•   Any other issue which, in the opinion of the study staff, may

○Put the participant or their contacts at risk because of participation in the study,○Adversely affect the interpretation of the study results, or○Impair the participant’s ability to participate in the study.

a: Participants discovered to have evidence of latent
*M. tb* infection as defined by a positive ELISPOT test will be referred for a plain chest x-ray. If there is any evidence of active TB disease either on clinical or radiological grounds, further investigation and treatment will be offered under the supervision of a consultant physician in respiratory medicine or infectious diseases.

b: Participants who are excluded from the study because they have been discovered to have a previously undiagnosed condition thought to require further medical attention will be referred appropriately to their GP or an NHS specialist service for further investigation and treatment.

c: Participants will be excluded from the study if they are concurrently involved in another trial that involves regular blood tests or an investigational medicinal product. To check this, participants will be asked to provide their National Insurance or Passport number (if they are a non-British citizen) and will be registered on a national database of participants in clinical trials (
www.tops.org.uk).

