### Description of study interventions and study procedures

**
Clinical assessment
**

Clinical assessment is conducted to confirm and ensure the participant is generally healthy.

•   
**Review of medical history:** The initial clinic visit will include a focused clinical history including obtaining information on any concurrent medical conditions, medications (including prescription, over the counter and illicit drug use) and vaccination history. Medical history may be confirmed with the GP records prior to the screen visit if there are any concerns or uncertainty remaining after the initial visit where eligibility has been assessed as indicated by the medical doctor.

•   
**Clinical examination:** The initial clinic visit will include a focused clinical history and targeted clinical examination including recording and evaluating vital signs including heart rate, blood pressure, temperature, oxygen saturations, auscultation of the lung fields and heart sounds. We will also measure weight and height, calculate BMI and estimate lean body mass.

Should a previously unrecognised abnormality be identified, this will be explained to the individual, and all relevant results will be forwarded to their GP so that appropriate investigations and follow-up can be arranged. Further participation will be determined at the discretion of the study doctor. If the participant has a positive HIV or hepatitis test, the result will be given by a suitably trained medical doctor and the participant will be referred to the local HIV/hepatitis service.

Participants may be re-screened at a later date to determine whether they meet eligibility criteria (e.g. if they have an acute infection on the date of screening that has subsequently resolved). They will be reimbursed for the additional study visit.

**
Clinical samples (obtained during study visits)
**

The following samples will be obtained during the study:

1.   
**Urine** – Participants will be asked to collect up to 20ml of urine at screening and vaccination visit for pregnancy testing (female).

2.   

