### Risk assessment

A risk assessment and monitoring plan will be prepared before the study opens and will be reviewed as necessary over the course of the study to reflect significant changes to the protocol or outcomes of monitoring activities. Specific risks are outline below.

**
Phlebotomy
**

The total amount of blood collected over the study period will be a maximum of 350mL. This amount should not compromise otherwise healthy participants. Risks occasionally associated with venepuncture include pain and bruising at the site of venepuncture, light-headedness, and syncope (rarely).

**
Nasal, nasopharyngeal and throat samples
**

This may cause some discomfort, eye watering or a small spot of blood. Participants may swallow the saline during nasal wash which may taste salty.

**
Challenge with BCG SSI
**

Full details are given in the summary of product characteristics (SmPC). In brief:

**
*Local reaction from intradermal BCG injection*
**

•   An inflammatory reaction as manifested by redness and swelling is expected to occur at the site of injection, followed by a local lesion that may ulcerate to be moist for up to three weeks. This heals over some weeks to months to leave a small flat scar. It is also possible to develop some swelling (<1cm diameter) of axillary lymph nodes.

•   Uncommonly (less than 1 in 100 people) swelling of axillary lymph nodes to more than 1cm across, or an ulcer that discharges fluid at the injection site may occur.

•   Rare side effects (less than 1 in 1000 people) include inflammation of lymph nodes leading to abscesses and discharge of fluid from the swellings.

**
*Systemic reactions*
**

•   Systemic reactions to BCG are rare (less than 1 in 1000 people) and include low-grade fever and headache, and allergic reactions. Disseminated complications of BCG, such as bone infections, have also been reported, but are extremely rare and have usually been reported in immunocompromised, not immunocompetent, individuals.

**
*Allergic reactions*
**

•   Allergic reactions from mild to severe may occur in response to any constituent of a medicinal product. Anaphylaxis is extremely rare but can occur.

**
Skin biopsy
**

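### The haemoglobin STOP limit is printed as 10 g/L (1.0 g/dL) and so excludes nobody in practice; a lesser fault is that causality is defined on four levels but classified on five

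*Protocol article*

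**What the plan says.** **Haemoglobin.** Table 3 (clinical assessment and STOP criteria) lists, among the full blood count limits, "STOP if Hb <10g/l". The limit is binding in two places. The exclusion criteria include "Participants who meet STOP criteria at the time of screening", and the Participant identification section says that if any STOP criteria "are met, the participant is excluded from and/or exits the study". Table 2 schedules the full blood count once, at screening. On blood volume, the Risk assessment says "The total amount of blood collected over the study period will be a maximum of 350mL" and adds "This amount should not compromise otherwise healthy participants".

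Other provisions rely on judgement. A separate exclusion covers "Any abnormality of screening blood or urine tests that is deemed to be clinically significant". A doctor signs off eligibility before the injection. If a new abnormality is found at clinical assessment, "Further participation will be determined at the discretion of the study doctor".

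**Causality.** The Causality assessment text under Safety reporting requires each adverse event to be judged against four defined levels: 0 no relationship, 1 unlikely, 2 likely, 3 definite. The printed criteria for level 2 end on a dangling *or*. The next paragraph ranks events on five levels, from definite through probable, possible and unlikely to not related, and says "Definite (4), probable (3) and possible (2) are considered to be related". Codes 0 and 1 are unrelated. Where the assessors differ, the greatest degree of relationship prevails.

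**The concern.** A STOP limit is meant to be an objective floor that does not depend on who is on duty. The haemoglobin limit as printed lies far below any value that a person attending an outpatient clinic would have, so the rule cannot do its job. It is also the only numerical protection against anaemia in a study that takes repeated blood samples and accepts the total volume on the ground that participants are healthy. The entry is complete and legible, so it does not look like damage from text extraction.

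The causality text gives an assessor criteria on one scale and asks for the result on another. A code of 3 is *definite* by the criteria and *probable* by the classification. A rule that the greatest degree prevails needs a common scale to work on. *Possible* is the lowest category counted as related, so it marks the boundary, yet nothing says what qualifies. Relatedness feeds the progression criterion on challenge-related serious events, reporting to the ethics committee, and follow-up of adverse events.

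**Working it through.** **Haemoglobin**

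Inputs: the limit of 10 g/L (Table 3); full blood count at screening only (Table 2); 50 mL per visit and a 350 mL maximum (Clinical samples; Risk assessment); seven visits, of which screening is the first (Table 7). Conversion: 1 g/dL = 10 g/L.

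1. The plan's blood total reproduces: 7 visits x 50 mL = 350 mL.
2. The printed limit in the other common unit: 10 g/L / 10 = 1.0 g/dL.
3. If 10 g/dL was intended (an assumption, since the article does not say so): 10 x 10 = 100 g/L. The printed limit is too low by a factor of 100 / 10 = 10.
4. Values that pass the printed rule but would fail a 100 g/L limit: 10 to below 100 g/L, that is 1.0 to below 10 g/dL.
5. Blood drawn after the sample that gives the haemoglobin result: 350 - 50 = 300 mL, or 6 x 50 mL. This is a ceiling. Table 2 lists blood assays after screening only on days 0, 2, 7 and 14, which would be 4 x 50 = 200 mL, whereas Table 7 marks blood at all seven visits.

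**Causality**

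| Code | Level where criteria are given | Level used to classify | Class under the five-level rule |
|---|---|---|---|
| 0 | none | none | unrelated |
| 1 | unlikely | unlikely | unrelated |
| 2 | likely | possible | related |
| 3 | definite | probable | related |
| 4 | not defined | definite | related |

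- Levels defined: 4. Levels used: 5.
- Codes with two meanings: 2 (codes 2 and 3).
- Codes in use without a definition: 1 (code 4).
- Labels without criteria: 2 (possible and probable).
- Labels with criteria but no place in the classification: 1 (likely).
- Cut between unrelated and related: between 1 and 2 on either numbering. An event coded on any of the four defined levels therefore keeps its class.

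**The case against.** The haemoglobin entry is probably a slip of unit that any clinician would read through, and several controls do not depend on the number: the exclusion for clinically significant abnormal results, the doctor's sign-off, and the study doctor's discretion. This stands in part. A reader might infer that severely anaemic volunteers would be enrolled, and the documents do not support that, because those controls could each stop it. But they are matters of judgement, and Table 3 exists to set a floor that is not. A reader might also take the whole 350 mL as following the check. It does not, because the screening sample is one of the seven.

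On causality the objection is stronger. The cut is the same on both scales, the greatest degree prevails, and the progression, reporting and follow-up rules turn on related versus unrelated and not on the grade. The data and safety monitoring committee reviews every serious event whatever its relatedness. So a reader who infers that related events would be undercounted, or that the progression decision would change, goes further than the text allows.

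Two further readings are tempting and should not be pressed:

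- One end-of-study follow-up rule uses the word *likely*, which is a label only on the four-level scale. It reads as ordinary English, and a general rule already requires follow-up of events considered related.
- The printed levels 2 and 3 ask for a BCG-like pattern, while the adverse reaction definition in Table 4 turns on whether a relationship can be ruled out. Level 2 is unfinished, so no firm contradiction can be drawn from it.

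**Conclusion.** The haemoglobin limit is wrong as printed and should be corrected. At 1.0 g/dL it excludes nobody in practice, and up to 300 mL of blood may follow. The factor of ten, and the band from 10 to below 100 g/L that passes, rest on the assumption that 10 g/dL was intended. That the printed value is inoperative does not depend on that assumption. Clinical discretion and sign-off reduce the practical risk without replacing the limit.

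The causality mismatch is real but minor. Its likely effect is uneven grading, for example a *definite* event recorded as *probable*, and uncertainty over which events count as *possible*. It does not move any event coded on the defined levels across the related/unrelated line.

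**What to change.** 1. **Table 3.** Correct the unit or value before anyone is screened, presumably to below 100 g/L (10 g/dL), with the clinical lead confirming the intended figure. Make the same check in the case report form.
2. **Causality.** Use one scale in both places. The simplest choice is the defined 0 to 3 scale, ranked definite, likely, unlikely, none, with 2 and 3 related and 0 and 1 unrelated.
3. **Level 2.** The sponsor should complete or delete the dangling *or*. The criteria for levels 1 and 2 should otherwise stay as they are: rewriting them could move the boundary between related and unrelated, which goes beyond removing the inconsistency.

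The cost is a wording amendment to the protocol and case report form, which under Modifications to protocol needs sponsor agreement and then ethical and regulatory approval. The Study status section says recruitment had not begun at submission, so at that point the change could be made before any participant was affected. Visits, samples and sample size stay the same.
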